### Adverse Events

Any adverse events, including symptoms, signs, and physical or laboratory examination abnormalities, will be carefully evaluated and recorded. Researchers will analyze the causes of these adverse events, make judgments, and track and record them in a timely manner. Once an adverse event occurs, doctors will provide the corresponding treatment to the patient for free. All adverse events will be judged for their characteristics, severity, and potential relationship to the study treatment. The correlation between adverse events and the study treatment is divided into 5 levels: definitely related, probably related, possibly related, possibly unrelated, and definitely unrelated. Based on the judgment and severity of adverse events, the primary investigator and ethics committee will be informed immediately to decide whether to discontinue observation, retain the medical records of participants who withdraw from the experiment, conduct a full data set analysis of the efficacy and adverse reactions, and fill in the experiment conclusion and the reason for case withdrawal.

### Data Collection and Management

An electronic information data collection system for our research has been created by the Institute of Traumatology, Shi’s Center of Orthopedics and Traumatology. All data will be electronic, double-checked, and backed up by 2 research assistants and entered into the system for mutual verification and correction of errors. Once all electronic data are verified against the original data, the data will be locked, and any modifications and their reasons will leave a trace in the data backend.

### Statistical Analysis

The main objective of this study is to evaluate the clinical effectiveness of SCRM therapy in patients with AJS. Additionally, secondary analyses will be conducted to assess changes in VAS scores, VSS-C scores, imaging findings, and cervical mobility before and after treatment in patients with AJS. Analyses will be performed using IBM SPSS 22.0. The measurement data will be expressed using mean differences (mean and standard deviation). The repeated measurement data will be analyzed using within-group variance analysis. Enumeration data will be presented as rates. The sample size needed for the Pearson chi-square test to compare rates between the 2 groups before and after treatment will be determined using the normal approximation algorithm and a 1-sided test. This study employs the superiority test that uses a 1-sided test level of α=.05. A *P* value of ≤.05 signifies the rejection of H0, thereby establishing the superiority of the SCRM group over the BCM group. Conversely, a *P* value >.05 indicates that a definitive conclusion regarding superiority cannot be drawn at this stage. The safety analysis will employ the chi-square test to compare the incidence of adverse reactions between the 2 groups. In instances where the data fail to meet the requirements of the chi-square test, the Fisher exact probability method will be employed.

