##### Imaging Changes of Cervical CT

All participants will undergo cervical CT examination at visits 0, 1, and 6. Two radiologists will measure the distance from the lateral mass of the atlantoaxial joint to the dentate process and the distance from the axis to the midline of the spinous process. Each radiologist will measure each image 3 times, and the average of the 6 outcomes will be taken as the final result. The improvement rate will then be calculated based on the results. The calculation formula is as follows:

Improvement rate = ([distance at pretreatment – distance after treatment] / distance at pretreatment) 100

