### Limitations

For classification, AJS has been divided into 8 types. For the different types, the SCRM techniques are different, while the BCM techniques are the same. As the incidence rate of AJS is not high, it may be difficult to recruit patients with each type of AJS, who meet the statistical requirements, in a limited time. Therefore, we will not separate the different AJS types, but instead combine them to observe the difference in efficacy between SCRM and BCM. In the future, we will further extend our project timeline and recruit as many subjects as possible for each type of AJS, so that efficacy analysis can be conducted for different types of AJS.

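### The repeated secondary outcomes are given only a within-group analysis, so they yield no SCRM-versus-BCM contrast; separately, the imaging improvement rate does not say which distance it uses

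*Protocol article*

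**What the plan says.** All of this is in the protocol article.

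- **Aim of the secondary analyses (Statistical Analysis).** The text says that "secondary analyses will be conducted to assess changes in VAS scores, VSS-C scores, imaging findings, and cervical mobility before and after treatment".
- **Method for repeated data (same section).** "The repeated measurement data will be analyzed using within-group variance analysis".
- **Between-group tests named (same section).** For efficacy, the section refers to the "Pearson chi-square test to compare rates between the 2 groups". For safety, it gives chi-square or Fisher tests of adverse reactions. The one-sided superiority rule follows the chi-square sentence and is not tied to any continuous outcome.
- **Purpose of the trial (Limitations).** With the AJS types pooled, the study is to "observe the difference in efficacy between SCRM and BCM".
- **Imaging (Imaging Changes of Cervical CT).** Two radiologists will "measure the distance from the lateral mass of the atlantoaxial joint to the dentate process" and also the distance from the axis to the midline. The outcome is then "Improvement rate = ([distance at pretreatment – distance after treatment] / distance at pretreatment) 100". No side is named, and the distance is not defined as a left-right difference.
- **Schedule (Table 1).** VAS and mobility are taken at baseline and every 4 weeks to week 24, VSS-C at baseline and weeks 4, 16 and 24, and imaging at baseline and weeks 4 and 24.

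**The concern.** A within-group analysis asks whether an arm changed over time. In this trial both arms receive the same relaxation therapy followed by a rotational manipulation, and patients enter with symptoms of less than 4 weeks. Natural recovery and regression to the mean will therefore contribute to change in both arms. A within-arm P value absorbs all of that and makes no use of the randomisation. Two significant arms say nothing about which is better, and one significant arm beside one non-significant arm is not evidence of a difference. This is more than a detail left to a later analysis plan, because a method has been stated and it does not answer the trial's question.

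The imaging outcome raises a separate question of definition. Under Diagnostic Criteria the abnormality is a left-right gap difference above 2 mm, so there is a wide and a narrow side. Recentring shortens one distance and lengthens the other. A rate computed on an unspecified distance can therefore take either sign for the same corrected joint.

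**Working it through.** The protocol gives no figure for any secondary outcome, so there is none to reproduce. Its 48 per group (Sample Size) belongs to the primary rate and is used here only as the arm size.

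**1. Within-arm tests against a between-arm test**

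Inputs:
- 48 per arm and dropout up to 20% (Sample Size): 48 × 0.80 = 38.4, so 38 per arm.
- Assumed, because the documents give no SDs: the same true change in both arms, baseline-to-follow-up correlation r = 0.5, and two-sided 0.05 paired t tests. The SD of change is then SD × √(2(1 − r)) = 1.0 SD.

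If each arm's within-group test has power p, the chance that exactly one arm is significant is 2p(1 − p), and the chance that both are is p². Power comes from the noncentral t distribution with n = 38.

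| True change, both arms | p | Exactly one arm significant | Both significant |
|---|---|---|---|
| 0.3 SD | 0.437 | 2 × 0.437 × 0.563 = 49% | 19% |
| 0.4 SD | 0.671 | 2 × 0.671 × 0.329 = 44% | 45% |
| 0.5 SD | 0.851 | 2 × 0.851 × 0.149 = 25% | 72% |
| 1.0 SD | 1.000 | 0% | 100% |

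A simulation of 20,000 trials gave 49%, 43%, 25% and 0% for exactly one arm. A direct between-arm test of change was significant in about 5% of the same trials at every size of change. With 48 per arm the simulated figures are 49%, 35%, 14% and 0%.

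On the VAS with an assumed SD of change of 22 mm and 38 per arm, the chance that exactly one arm is significant is 48% for a common fall of 8 mm, 34% for 10 mm, 17% for 12 mm, 3% for 15 mm and about 0% for 20 mm. At 20 mm both arms are significant in over 99% of trials.

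**2. Imaging formula**

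The rate is (pre − post)/pre × 100. The distances below are assumed, and each case is a perfect recentring.

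| Wide / narrow gap, pre → post (mm) | Wide side | Narrow side | Absolute left-right difference |
|---|---|---|---|
| 5 / 2 → 3.5 / 3.5 | (5 − 3.5)/5 = +30% | (2 − 3.5)/2 = −75% | (3 − 0)/3 = +100% |
| 4.5 / 2.5 → 3.5 / 3.5 | +22% | −40% | +100% |
| 6 / 3 → 4.5 / 4.5 | +25% | −50% | +100% |

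The same joint scores anywhere from −75% to +100% according to a choice that the text leaves open. A fixed anatomical side does not settle it: under SCRM Technique the wide side is the left in type A and the right in type B.

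For the midline offset with baseline value b, a shift of e mm in the follow-up reading moves the rate by 100 × e/b. This grows without limit as b approaches 0, and the rate is undefined at b = 0. SCRM Technique describes types A and B as having the spinous process on the midline.

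**The case against.** **The phrase may be loose English for repeated-measures ANOVA**, which can carry a group-by-time term, and the same paragraph speaks of superiority of SCRM over BCM. This lowers certainty about intent. But no group or group-by-visit term is named, and the before-after framing of the secondary analyses favours the literal reading. The sentence needs correcting on either reading.

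**The 49% is close to the ceiling.** 2p(1 − p) cannot exceed 50%, and the figure falls to about 0% for large changes. The Introduction reports a 50% VAS fall immediately after SCRM, which points towards large changes. At one-sided 0.05 the 8 mm case gives 41%. This stands, so the range should be cited and not its top. With large changes the problem takes another form: both arms are significant and nothing is learned about their difference.

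**A reader might infer that the imaging formula definitely takes the wrong sign.** The article does not support that. It never says that the narrow side is scored, and its only averaging is over the six readings. If the wide side or the left-right difference is meant, the sign fault disappears. What stands is that the distance is undefined.

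**The near-zero midline offset relies on types A and B.** Diagnostic Criteria, read literally, requires misalignment as well as asymmetry, which would exclude those types. SCRM Technique and Limitations keep all eight. These sections must be reconciled, and the instability is conditional on that.

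**A reader might also infer that the imaging formula invalidates every secondary comparison.** It has no bearing on VAS, VSS-C or mobility, and a per-patient rate could be compared between arms.

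**Conclusion.** The point holds for VAS, VSS-C and cervical mobility: the only analysis stated for them is within-group, and it provides no randomised comparison of SCRM with BCM. With equal true change, 38 per arm and r = 0.5, separate within-arm tests disagree in about 0% to 49% of trials, against about 5% for a between-arm test. The percentages depend on the assumed change and SD. The absence of a between-arm contrast does not.

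For imaging, the supported finding is narrower. The distance entering the rate is unspecified, the rate would be reversed if the narrow side were used, and the midline percentage is unstable where the baseline offset is near zero.

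It would be wrong to conclude that the trial lacks a between-group test. The primary efficacy rate and adverse reactions have one, and the main conclusion does not rest on the outcomes discussed here. The point should be fixed, with high confidence on the missing contrast and moderate confidence on imaging.

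**What to change.** 1. Replace the within-group sentence with a between-group repeated-measures analysis for VAS, VSS-C and each mobility angle. One suitable form is a mixed model with group, visit, group × visit and the baseline value. Report the SCRM minus BCM difference with 95% CI at weeks 4 and 24, and for VSS-C at its scheduled visits (weeks 4, 16 and 24). A repeated-measures ANOVA with an explicit group-by-visit contrast would also meet the core objection. Within-arm changes can stay as description.
2. Define the imaging outcome as the absolute left-right difference in lateral mass-dens distance (mm) and the absolute spinous-process offset (mm). Compare the arms at weeks 4 and 24 adjusting for baseline, and keep percentages descriptive.
3. Reconcile Diagnostic Criteria with the type definitions under SCRM Technique, so that it is clear which baseline values can occur.

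The cost is a documented change of wording, made before the allocation is revealed to the analyst. No new visits or measurements are needed for VAS, VSS-C or mobility. For imaging, both sides must have been recorded; if only one was, the stored CT images would have to be re-measured.

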### Sample Size

The sample size calculation is based on our previous clinical research in patients with cervical spondylosis of the nerve root type, using the same primary outcome instrument. The efficiency of SCRM is 89.5%, while that of BCM is 54.6%. The sample size calculation formula is as follows:

The α is .05 and 1–β is .90. According to estimations, 48 participants per group are needed considering that this is a long-term follow-up that is expected to have a dropout rate of no greater than 20%.

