#### Primary Outcome

##### Efficacy Rate

The clinical symptoms of all subjects will be recorded and evaluated using the numerical rating scale (NRS), which is composed of a horizontal line having a length from 0 to 10 cm, with “0” indicating “normal” and “10” indicating “unbearable.” We will refer to the efficacy evaluation standards in the “Diagnostic and Therapeutic Efficacy Standards for Traditional Chinese Medicine Diseases” issued by the China Administration of Traditional Chinese Medicine in 1994.

We define clinical cure as a decrease of more than 80% in the NRS score for clinical symptoms and the ability to live and work normally. We define clinical improvement as a decrease of 20% to 80% in the NRS score for clinical symptoms. We define clinical cureless as a decrease of less than 20% in the NRS score for clinical symptoms. We define clinical recurrence as the reappearance of the original symptoms after treatment, with the degree being equivalent to or greater than that before treatment.

All patients will be followed up, and the efficacy rate will be calculated at visit 1 after the intervention. The efficacy rate and clinical recurrence rate will be calculated at visit 6. The calculation formulas are as follows:

Efficacy rate = ([number of clinical cure cases + number of clinical improvement cases – number of clinical cureless cases] / total number of patients) 100

Clinical recurrence rate = (number of clinical cureless cases / [number of clinical cure cases + number of clinical improvement cases]) 100

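### The efficacy rates are to be compared by an unadjusted chi-square although response is a percentage of the baseline NRS; pre-specified adjustment for that score would be a cheap, modest gain in efficiency, not the repair of an error

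*Protocol article*

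**What the plan says.** Protocol article, Statistical Analysis: the only test named for the efficacy rates is the "Pearson chi-square test to compare rates between the 2 groups before and after treatment". No covariate, stratum or model is mentioned. The decision rule is fixed in the same place: "This study employs the superiority test that uses a 1-sided test level of α=.05", with superiority claimed at P ≤ .05.

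Protocol article, Efficacy Rate: patients are classed by percentage change from their own baseline, for example "We define clinical improvement as a decrease of 20% to 80% in the NRS score for clinical symptoms". Cure lies above that band and failure below it.

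Protocol article, Study Design and Table 1: symptoms and signs, and imaging, are recorded at visit 0, before treatment.

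Protocol article, Randomization and Allocation: arms are assigned by odd and even random numbers, and no stratification is described.

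Protocol article, Limitations: "we will not separate the different AJS types, but instead combine them to observe the difference in efficacy between SCRM and BCM".

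Protocol article, Sample Size: "48 participants per group are needed", from rates of 89.5% and 54.6% with up to 20% dropout; "The α is .05 and 1–β is .90".

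**The concern.** The outcome is computed from a baseline value that every patient has, yet that value plays no part in the comparison. If baseline NRS predicts response, an unadjusted test leaves explainable variation in the error term. A chance difference in baseline severity between arms then passes into the estimated treatment difference. As described, neither the allocation nor the analysis limits this. At stake are some precision and an easy answer to a later question about baseline imbalance. The validity of the P value is not at stake.

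**Working it through.** **1. The planned figure.** Inputs from Sample Size: p1 = .895, p2 = .546, d = .349, power .90.

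- Mean rate = .7205, so 2 × .7205 × .2795 = .4028 (root .6346). Also .895 × .105 + .546 × .454 = .0940 + .2479 = .3419 (root .5847).
- n = [z_α × .6346 + 1.2816 × .5847]² / .349².
- One-sided .05: (1.0439 + .7493)² / .1218 = 26.4, so 27; with continuity correction 32. After 20% dropout: 34 or 40.
- Two-sided .05: (1.2439 + .7493)² / .1218 = 32.6, so 33; with continuity correction 39. Then 39/.8 gives 49, and 39 × 1.2 gives 47.

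Of the forms tried, only the two-sided, continuity-corrected one comes within 2 of the stated 48. The sidedness mismatch is a separate point. Below I use the one-sided test that Statistical Analysis states.

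**2. Power of the plan as written.** Evaluable per arm: 48 × .8 = 38.4, so 38.

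- z = (.349 − 1.645 × √(.4028/38)) / √(.3419/38) = (.349 − .1693)/.0949 = 1.89, so power is .971.
- With all 48 per arm, power is .991.

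**3. What adjustment could gain.** The article gives no prognostic strength, so it has to be assumed: logit P(response) = a_arm + b·z, with z the standardised baseline score, b = 0, 0.5 or 1.0 (odds ratio 1.0, 1.65 or 2.7 per SD), and intercepts set to keep the marginal rates.

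Hand check: since Cov(response, z) is at most b·p(1−p), the share of variance that linear adjustment can remove is at most about b²·Σ[p(1−p)]²/Σp(1−p) = b² × (.0088 + .0614)/.3419 = .21b². That is 5% at b = 0.5 and 21% at b = 1.0. These are ceilings.

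Simulation, 2,000 trials per scenario, one-sided .05. Power compares the pooled z test (equivalent to the chi-square) with a covariate-adjusted logistic score test. The variance ratio compares the standardised with the raw risk difference.

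| Odds ratio per SD (assumed) | Variance ratio, all scenarios | Power, .895 v .546, 38 per arm | Power, .80 v .546 (assumed), 48 per arm |
|---|---|---|---|
| 1.0 | 1.01-1.02 | .972 → .971 | .850 → .846 |
| 1.65 | .96-.99 | .966 → .973 | .865 → .869 |
| 2.7 | .85-.90 | .974 → .990 | .864 → .906 |

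A second simulation with baseline NRS as the only covariate, 38 per arm, gave variance ratios of about 1.01, .95-.98 and .84-.89. Its type I error was 4.4-5.4%, and power at the planned rates went from 97% to 97-98%.

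In plain terms, a ratio of .85 makes the interval 1 − √.85 = 8% narrower, equivalent to 38/.85 = 45 unadjusted patients per arm.

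**4. How much the percentage definition alone implies.** With rating-error SDs of 0.5 to 1.5 and proportional or absolute change models (all assumed), the built-in log odds ratio per SD ran from −.17 to .47, that is an odds ratio of 0.84 to 1.6. The range includes no effect. The construction of the endpoint therefore supports only the 1.65 row at best; anything larger needs severity to be truly prognostic.

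**5. Validity of the unadjusted test.** With equal rates (.70 v .70) and b up to 1.0, the unadjusted test rejected in 4.4-6.2% of trials and the adjusted score test in 4.6-6.4% (Monte Carlo SE √(.05 × .95/2000) = 0.5 points). The two moved together, so neither is favoured on this ground.

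**6. Can the data carry the model?** Expected non-responders: 38 × (.105 + .454) = 21, or 48 × .559 = 27. Arm and baseline NRS are two terms, so about 11 to 13 non-responders per term.

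**The case against.** **It is a preference.** The chi-square is valid under randomisation, its standard error already allows for chance imbalance, and covariates are often left to an analysis plan not shown here. The quoted words also sit in a sentence about sample size. The validity argument stands in full: a reader might infer that the primary test is biased or its error rate inflated, and the documents do not support that. But this is the only sentence naming a test for the efficacy rates, and the decision rule follows it, so the unadjusted comparison is a stated choice and can be commented on.

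**The gain is hypothetical.** This stands as a limit on size. A reader might infer that precision is certainly being lost, or that power would rise by many points. The article gives no prognostic strength; a variance reduction near 25% needs an assumed odds ratio of about 4.5 per SD.

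**Power is already 97%.** True at the planned rates. Those rates, however, come from nerve-root-type cervical spondylosis, which the Exclusion Criteria rule out here, so a smaller difference is possible. That is where adjustment would show.

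**AJS type should then be adjusted for too.** A reader might infer this, because type decides the SCRM technique. It does not hold for the primary model:

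- Diagnostic Criteria, read literally, require both a gap difference above 2 mm and spinous-process misalignment, so every eligible patient would be of mixed type. SCRM Technique nevertheless defines gap-only and rotation-only types.
- Adding three non-prognostic type groups let type I error drift to about 5.6-6.3% when the baseline score was weakly prognostic or not at all.
- Only 38 × .105 = 4 SCRM non-responders are expected. With three equal groups, about 60% of simulated trials at the planned rates had an SCRM group with none.
- BCM does not depend on type, so nothing shows that type was recorded in that arm. Typing before allocation is no longer possible for the 76 patients enrolled by May 2024.

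The reason given in Limitations, too few patients per type, is an argument against separate analyses by type. It does not bear on adjustment for baseline NRS.

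**The endpoint needs attention first.** The printed efficacy-rate formula subtracts failures, so it is not a proportion that a chi-square can compare. This stands as a separate point; any test, adjusted or not, needs a responder definition for each patient.

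**Conclusion.** The point holds as a recommended improvement. The named primary test ignores a baseline score from which the outcome itself is computed and which costs nothing to use. The expected effect runs from a 1-2% rise in variance if baseline NRS is not prognostic to a fall of about 15% at an odds ratio of 2.7 per SD. Power barely changes at 89.5% v 54.6%. At an assumed 80% v 54.6% with 48 per arm it changes by 0 to about 4 points. These sizes rest on assumed prognostic strength, a logistic relation and, at the planned rates, 38 evaluable patients per arm. The planned chi-square is not wrong, and the case does not extend to AJS type in the primary model.

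**What to change.** Before unblinding, state in Statistical Analysis that the primary comparison of responders (clinical cure or improvement) with non-responders uses a logistic model with arm and baseline symptom NRS. Report it as a standardised risk difference with confidence interval, and keep the Pearson chi-square as a supportive analysis.

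Leave AJS type group out of the primary model. Use it at most in a supportive analysis, once Diagnostic Criteria and SCRM Technique are reconciled on whether gap-only and rotation-only patients are eligible.

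Cost: a few lines of text and code, a dated record that the change preceded unblinding, and no new data, since visit 0 already supplies the score. If an analysis plan already specifies such a model, the article's wording only needs to agree with it. If unblinding has already happened, the adjusted result should be labelled supportive.

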### Diagnostic Criteria

The diagnosis of AJS is based on the Diagnostic Criteria for Traditional Chinese Medicine and the International Classification of Diseases 11th Revision (ICD-11), and several aspects are considered. First, the patient has a history of neck strain or injury and has a long-term habit of working or living with a low head. Second, the clinical manifestations are mainly vertigo, dizziness, headache, and soreness in the neck. Third, the cervical movement is mainly limited to the left-right rotation of the atlantoaxial joint. When performing palpation, the muscle tension around the atlantoaxial joint increases or small blocky or strip-shaped muscle nodules are felt, which may induce or exacerbate dizziness or vertigo. Fourth, cervical X-ray or CT shows an asymmetrical gap between the lateral mass of the atlantoaxial joint and the odontoid process, with a difference of more than 2 mm, along with the misalignment of the axis of the spinous process relative to the midline of the spinous process.

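### The only stated safety comparison counts adverse reactions, an undefined term, although the protocol records all adverse events; the main comparison should be on all recorded events

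*Protocol article*

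**What the plan says.** The Objective in the Abstract puts efficacy and safety together as the principal aim. The Abstract's Methods paragraph lists adverse events among the monitored indicators, and Table 1 (Study Design) schedules them at visits 1 to 6.

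The Adverse Events section sets a wide net: "Any adverse events, including symptoms, signs, and physical or laboratory examination abnormalities, will be carefully evaluated and recorded". On cause it says: "Researchers will analyze the causes of these adverse events, make judgments, and track and record them in a timely manner". The link between event and treatment is "divided into 5 levels: definitely related, probably related, possibly related, possibly unrelated, and definitely unrelated".

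The Statistical Analysis section then states one between-group comparison for safety: "The safety analysis will employ the chi-square test to compare the incidence of adverse reactions between the 2 groups". The fallback for sparse data is also given: "In instances where the data fail to meet the requirements of the chi-square test, the Fisher exact probability method will be employed". No comparison of all adverse events by arm is stated.

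**The concern.** What is collected and what is compared carry different names, and in safety work the two names usually mean different things. An adverse event is anything untoward that happens; an adverse reaction is an event attributed to the treatment. If that usual meaning applies, a judgment about cause stands between the recorded data and the test.

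The judgment is hard to make in this trial. Under Diagnostic Criteria, "the clinical manifestations are mainly vertigo, dizziness, headache, and soreness in the neck", and the Inclusion Criteria name much the same symptoms. A patient who becomes dizzier or has more neck pain after a rotational manipulation may have been harmed, or may be showing the disease. If such an event is graded as possibly unrelated, a related-only count omits it. The trial could then report on safety without comparing the arms on the very events that are hardest to attribute.

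**Working it through.** The article states no rate, power or sample size for safety, so there is no figure to reproduce. The check is a comparison of its own passages, followed by a short argument about direction.

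**Step 1. Which term is used where.**

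| Place | Term | Role |
|---|---|---|
| Abstract, Methods | adverse events | monitored indicator |
| Study Design, Table 1 | adverse events | scheduled at visits 1 to 6 |
| Adverse Events, most of the section | adverse events | recorded and graded |
| Adverse Events, last sentence | adverse reactions | object of an analysis: "conduct a full data set analysis of the efficacy and adverse reactions" |
| Withdrawal Criteria, item 1 | adverse reactions | reason for withdrawal |
| Statistical Analysis | adverse reactions | the between-group test |

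Collection is on one term and the test is on the other.

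**Step 2. Is there a bridge between the terms?** The scale has 5 levels ("definitely related, probably related, possibly related, possibly unrelated, and definitely unrelated"). Nothing says at which level an event becomes an adverse reaction, or that all levels count. The numerator of the stated test is therefore open. A count of all events and a count of related events would both comply with the text.

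**Step 3. Can AJS-like events fall outside a related-only count?** Yes. The symptoms in the Diagnostic and Inclusion Criteria are also plausible complaints after neck manipulation. The article also has other places to put worsening symptoms: item 2 of the Withdrawal Criteria covers symptoms that persist or progress, separately from adverse reactions in item 1, and the Primary Outcome section treats the return of original symptoms at equal or greater severity as clinical recurrence.

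**Step 4. What each count estimates.** Let *b* be the proportion of patients with background events, which randomisation makes equal in expectation in the two arms. Let *c*(SCRM) and *c*(BCM) be the proportions with events caused by treatment. Ignoring patients who have both kinds:

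- All events: (*b* + *c*(SCRM)) − (*b* + *c*(BCM)) = *c*(SCRM) − *c*(BCM). The full difference is kept, but *b* adds noise.
- Related events only, with a share *m* of caused events recognised as such in each arm and all background events correctly set aside: *m* × (*c*(SCRM) − *c*(BCM)). The noise goes, but only the share *m* of the difference remains.

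For events that look like AJS symptoms, *m* is exactly what is in doubt. The all-event comparison does not depend on it. The related-only count is the sharper one if attribution is accurate, so it deserves a place as a second table.

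**Step 5. Size.** The article gives no value for *b*, *c* or *m*. Only the direction follows from the text; a numerical effect does not.

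**The case against.** The best reply is that adverse reactions is simply a loose synonym here. The term is never defined, and it appears in the Adverse Events section in a sentence about handling adverse events. With adverse events named as the monitored item in the Abstract and Table 1, the Statistical Analysis sentence can fairly be read as covering all of them. This stands as far as it goes: the filter is one reading, not a stated rule. It does not dispose of the point, because a related-only test would comply just as well.

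A second reply is that an article may leave the cut on the relatedness scale, and the layout of safety tables, to the full protocol or analysis plan, which are not shown. That is accepted, and the missing cut alone would not be a finding. What remains is that the article does name the event type for its safety test, and the name differs from what it collects.

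Third, all events are recorded and count data are to be presented as rates, so an unfiltered count could still be reported. Symptoms and neck pain scores are also taken at every visit, and vertigo scores at weeks 4, 16 and 24, so worsening would show in the efficacy data. Both are true, but neither is a stated safety comparison.

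A reader might also infer that cause is judged by someone who knows the allocation, because the Blinding section does not list the researchers who judge it. The text does not support that. Researchers is a general word that may include the blinded outcome assessors; the Follow-Up Period section has those assessors set up the group in which events are reported; and only the manual therapists are said to be unblinded.

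**Conclusion.** The point holds as a mismatch that the document itself contains: all adverse events are recorded and graded, but the only stated comparison is on an undefined narrower-sounding term, in a trial whose principal aim includes safety. It should be corrected, and a definition alone is not enough. Defining adverse reactions as related events would settle the wording and leave the trial with no stated comparison free of causal judgment.

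The conclusion rests on one assumption: that a reader or analyst may take adverse reactions in its usual sense. It does not rest on the claim that events will be removed, which the article does not say. Nor can a shrinkage of the risk difference be quoted, since no adverse event rate or share judged related is given.

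**What to change.** In Statistical Analysis, state that the main safety comparison is the proportion of patients in each arm with at least one recorded adverse event, regardless of relatedness, using the chi-square or Fisher exact test already named. Add a second table, by arm, of events graded definitely, probably or possibly related. If the term adverse reactions is kept, tie it to those three levels and use it only for the second table.

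The definition of a recorded adverse event need not change. A reader might want every worsening above the visit 0 level counted as an event, but that would count ordinary fluctuation of a recurrent condition and overlap with the efficacy outcomes; the point does not depend on it.

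The cost is a few words and one table, with no new data. The downsides are higher reported event rates in both arms and possible dilution of a treatment-related difference by background events, which the second table is there to address. The change is best made before allocation is revealed to the statistician.
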